**Fig. 1 Fig1:**
[figure not shown]
Flowchart of the recruitment of patients *(C/B)RT* chemo or bioradiation, *M0* measurement before (C/B)RT, *M1* measurement after 12 weeks, *M2* measurement after 6 months, *M3* measurement after 12 months, *PEI* physical exercise intervention

#### Physical exercise intervention

All patients will receive usual physical exercise care. Usual care contains advise to exercise based on the ‘Dutch physical activity guideline’ [28]. This guideline advises adults to do 150 min of moderate intensive movement a week, and twice a week muscle and bone strengthening exercises. Patients who are randomised in the PEI group and accept the invitation to undergo the experimental intervention, receive a PEI for 10 weeks. The PEI will be executed 6 to 7 weeks during and 3 to 4 weeks after (C/B)RT. The PEI will be given at Medifit Fysiotherapie Instituut Verbeeten. The PEI consists of a 60 min intervention twice a week and will be supervised by a physiotherapist specialized in oncology. The PEI consists of both endurance exercises and resistance exercises. This PEI is based on two previous studies [13, 18]. During every intervention, the physiotherapist will register which endurance and resistance exercise is performed and how many sets, repetitions and which resistance per exercise is used.

Every exercise intervention starts and stops with a 10 min endurance exercise using the home trainer or treadmill. To preserve the exercise stimulus of the endurance exercises, patients will be asked to rate the endurance exercises on the 6 to 20 Borg rating of perceived exertion (RPE) [34]. A moderate to hard intensity level of these exercises are aimed, so a score between 12 and 16 RPE has to be achieved. The intensity of endurance exercise may progress over time, but may also be reduced as necessary according to the patient’s symptom burden.

Resistance exercises for the lower and upper extremity will consist of: calf raises, leg presses, lunges, squats, seated rows, lateral pull downs, bicep curls, and triceps extensions. At every PEI appointment, all resistance exercises will be executed. Before starting the PEI, muscle power is measured by a twelve repetition maximum (12RM). At the start of this program, patients will start with their 12RM score and perform 2 sets of 12 repetitions. Efforts will be made to have the exercise to rest ratio on 1 to 10, based on the duration of work period [5]. When the exercises become too easy, resistance can be increased by 5 to 10% of the 12RM. On the other hand, if it is too difficult for a patient to maintain their 12RM, for example due to symptom burden, it is acceptable to do exercises at a lower base of 5 to 10% of the 12RM.

Home-based endurance and resistance exercises three times a week is also part of the PEI. Instructions and an exercise diary will be provided by the physiotherapist at the first appointment. The patients will be asked to fill in this diary after every exercise session at home. This diary will be discussed weekly with the patient by the physiotherapist to repeat instructions and encourage the patient to continue exercising at home as much as needed. Endurance exercise contains a 30 min walking schedule. Resistance exercises are based on the exercises patients can perform without instruments: calf raises, squats, lunges and wall sits for lower extremity, and push-ups against the wall, side raises and front raises for upper extremity. Patients start with 2 sets of 12 repetitions. Self-efficacy has shown to have an impact on health practices and adaptation to cancer and cancer treatment [35]. By combining supervised exercising with individual home based exercises we aim to increase self-efficacy.

### Measurements

The socio-demographic data (age, gender, education, employment and marital status) and medical data (tumour site, disease stage, comorbidity, HPV status, tobacco and alcohol use, nutrition status and type of treatment) will be assessed at baseline (M0). Physical performance, muscle strength, fatigue, QoL, BMI, nutritional status, and physical activity will be assessed at baseline (M0), 12 weeks (M1) and 6 (M2) and 12 (M3) months after baseline. Treatment tolerability will be assessed at M1, M2 and M3. Health related costs will be collected at M3. All tests and Dutch questionnaires are validated and have satisfying clinimetric properties.

### Primary outcome

Physical performance will be measured by the 6MWT [36]. The 6MWT measures the walking distance in meters of a patient in 6 min on a 10 m parkour.

### Secondary outcomes

Muscle strength will be assessed by grip strength [37], lower and upper body strength and the 30 s chair stand test (30SCST) [38] according the standard procedures of these tests. We developed a measurement protocol how to perform the measurements. For the grip strength [kg], the JAMAR^®^ grip strength dynamometer will be used [37]. To assess lower (knee flexion and extension) and upper body strength [N] (elbow flexion and extension), the microFET^®^ hand held dynamometer will be used according to standardized procedures by 3 times testing [39]. The 30SCST will measure the number of completed stand ups on the patients’ fastest pace over a 30-second period.

Fatigue will be measured using the multidimensional fatigue inventory (MFI) which is a 20-item questionnaire assessing five dimensions: general, physical and mental fatigue, and reduced activity and motivation [40].

The following questionnaires will be used to measure QoL: the European organisation for research and treatment for cancer quality of life questionnaire (EORTC QLQ-C30), the EORTC QLQ head and neck module (EORTC QLQ-H&N43), and the EuroQol- five dimensions- five level (EQ-5D-5 L). The EORTC questionnaires are designed to be cancer-specific, multidimensional in structure, appropriate for self-administration and applicable across a range of cultural settings. The EQ-5D-5 L is a standardized instrument which can be used as a quantitative measure of health outcome and reflects the patient’s own judgement. Dutch reference values are available [41–43].

Height and weight in light clothing will be measured, from which body mass index (BMI) in kg/m^2^ will be calculated [44].

The short nutritional assessment questionnaire (SNAQ) consists of three questions and will be used to monitor nutritional status and assess the risk of malnutrition [45].

Physical activity will be measured by the short questionnaire to assess health enhancing physical activity (SQUASH), including commuting activities, leisure time activities, household activities, and activities at work and/or school [46].

(C/B)RT tolerability will be retrieved from medical records and registered as the percentage of scheduled treatment completion, percentage of (C/B)RT adjustment and type of (C/B)RT adjustment. Furthermore, toxicity will be registered from medical records, which includes the presence of pain, mucositis, dysphagia, aspiration, nausea and vomiting, and dry mouth according to the common terminology criteria for adverse events v 4.0 (CTCAE). To assess health related costs, a cost-effectiveness analysis will be performed for one year. Treatment data will be retrieved from medical records. Price levels of the years during this study will be used. By using the EQ-5D-5L and health related costs, the quality-adjusted life years (QALYs) can be calculated.

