## Background

In 2021, the incidence of head and neck cancer (HNC) in the Netherlands was 3,174 and the prevalence was 10,635 [1]. HNC includes tumours located in four anatomical sites: pharynx, larynx, oral cavity, and sinonasal cavity [2]. The most prevalent causes of HNC are heavy consumption of tobacco and/or alcohol, and the human papillomavirus (HPV) [2].

Treatment of HNC by radiotherapy (RT), chemoradiation (CRT) or bioradiation (BRT) can cause early side effects like mucositis, odynophagia, dysphagia, xerostomia, orofacial pain, laryngeal radio necrosis, dermatitis, hair loss, nausea, and vomiting [3]. Those early side effects can cause inadequate nutrition and hydration, which can lead to loss of muscle mass, loss of muscle strength, increased fatigue, decreased physical performance, and a decreased quality of life (QoL) [4, 5]. Physical exercise interventions (PEIs) primarily focusing on resistance training have proven effective in enhancing various health-related, physiological, and disease specific outcomes like early side effects [5–7]. However, the existing evidence suggests that resistance training alone may not suffice. Therefore, incorporating endurance training into the regimen appears to be beneficial [7]. Endurance training can reduce fatigue, improve QoL, and improve physical function [7]. For an optimal effect of both resistance and endurance exercises, it is necessary to train on a moderate to hard load and intensity [8]. Thereby, it is of importance to set the PEI volume on the patient’s physical performance at the start to be able to adapt the exercise intensity depending on progress, deterioration, and symptom burden during the PEI.

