### Statistical analyses

To test normality of continuous data, the Shapiro-Wilk test will be used. Continuous data will be presented descriptively with means and SDs. When continuous data are not normally distributed, the median and inter quartile range (IQR) will be presented. For ordinal data, both the median and IQR will be presented. Nominal data will be presented as numbers and percentages. Comparison between normally distributed groups will be done with the independent t-test when data are normally distributed. For non-normally distributed data, the Mann-Whitney U test will be used. Nominal data will be compared by the Chi-square test or Fisher-exact test when a particular cell is < 5. For all different groups, statistical analyses will be performed for intention-to-treat (ITT) and instrumental variable analysis [47]. An interim analysis will be conducted after 26 patients underwent the PEI to evaluate the power calculation. The incremental cost-effectiveness ratio (ICER) will be calculated as the difference in costs divided by the difference in QALYs between groups. When data are missing, ‘available case analyses’ will be used, indicating that missing cases will be discarded in the variables that are needed for a specific analysis. All analyses will be performed using statistical package for the social sciences (SPSS). A *p*-value below 0.05 is considered statistically significant.

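### Toxicity is recorded as presence of six symptoms, with no baseline value and no stated look-back window, so read literally a change in severity cannot register

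*Protocol article*

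**What the plan says.** Treatment tolerability is one of the study's named aims. The Secondary outcomes section gives it two parts, both taken from medical records.

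- Treatment delivery is "registered as the percentage of scheduled treatment completion, percentage of (C/B)RT adjustment and type of (C/B)RT adjustment".
- For toxicity, "toxicity will be registered from medical records, which includes the presence of pain, mucositis, dysphagia, aspiration, nausea and vomiting, and dry mouth", with CTCAE version 4.0 as the reference. The sentence does not mention grade.

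The Measurements section says "Treatment tolerability will be assessed at M1, M2 and M3". Physical performance, strength, fatigue, quality of life, BMI, nutritional status and physical activity, by contrast, "will be assessed at baseline (M0), 12 weeks (M1) and 6 (M2) and 12 (M3) months after baseline". The article does not say what period the M1 record of toxicity covers.

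The Statistical analyses section says "Nominal data will be compared by the Chi-square test or Fisher-exact test when a particular cell is < 5". It also describes ordinal data by median and IQR and names the Mann-Whitney U test for non-normal data.

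**The concern.** Presence is a yes/no variable, whereas CTCAE is a graded scale. If the extractor does what the sentence says, severity is lost and each item goes to the chi-square or Fisher test. The Background says that treatment "can cause early side effects like mucositis, odynophagia, dysphagia, xerostomia, orofacial pain". For symptoms of this kind, an exercise programme might make them milder without abolishing them, and a presence variable cannot show that.

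Two further points are left loose. The first is the period that M1 refers to. The second is the missing M0 record: pain and dysphagia can come from the tumour before any treatment, and would then be counted as toxicity.

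At stake is whether a null toxicity result can be interpreted. No other outcome is scheduled between M0 and 12 weeks, so the medical record is the only planned source on severity during treatment.

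**Working it through.** **1. Where M1 falls.** The Physical exercise intervention section says "The PEI will be executed 6 to 7 weeks during and 3 to 4 weeks after (C/B)RT", so (C/B)RT lasts 6 to 7 weeks. M1 is 12 weeks after baseline. Patients may consider participation until one week before treatment, so I assume that baseline lies 0 to 1 week before the first fraction.

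- Shortest gap from end of treatment to M1: 12 − 1 − 7 = 4 weeks.
- Longest gap: 12 − 0 − 6 = 6 weeks.

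If M1 means the state at the visit, the treatment weeks are not captured. If it means any occurrence since baseline, they are captured, but a brief mild episode counts the same as a severe one. Neither reading measures severity during treatment.

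**2. The plan's own figures.** No rate, effect or power is stated for toxicity. The arm size and acceptance rate come from the 6MWT calculation, which reproduces:

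- SD = √((88.24² + 110.26²)/2) = 99.86, and d = (483.16 − 374.52)/99.86 = 1.088. A two-sample t-test with 80% power and two-sided 0.05 needs 14.3, so 15.
- 15/(1 − 0.24) = 19.7, so 20. Then 20/0.36 = 55.6, so 56 per arm and 112 in total.

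**3. What presence coding costs.** All symptom rates here are assumptions. The inputs are 56 per arm, no drop-out, and control grades 0 to 4 in these percentages:

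- A: 5/15/40/38/2 (presence 95%)
- B: 20/30/30/18/2 (presence 80%)
- C: 40/30/20/8/2 (presence 60%)

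The exercise effect is a common odds ratio of 0.4 on P(grade ≥ k). For presence in A, the odds are 0.95/0.05 = 19, then 19 × 0.4 = 7.6, giving 7.6/8.6 = 88.4%. The same step gives 61.5% in B and 37.5% in C. If only acceptors benefit, the invited arm's distribution is 0.36 × shifted + 0.64 × control. Presence in A is then 0.36 × 88.4 + 0.64 × 95 = 92.6%.

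Presence was tested by chi-square, or by Fisher when a cell was below 5. Grade was tested by Mann-Whitney. There were 2,000 simulated trials, so the standard error is at most √(0.25/2000) = 1.1 points.

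| Control presence | All treated: presence | All treated: ordinal grade | 36% accept (ITT): presence | 36% accept (ITT): ordinal grade |
|---|---|---|---|---|
| 95% (A) | 13% | 75% | 3% | 16% |
| 80% (B) | 58% | 74% | 14% | 17% |
| 60% (C) | 67% | 73% | 12% | 13% |

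With an odds ratio of 0.5 and all treated, presence against ordinal grade gives 6% against 51% (A), 36% against 52% (B) and 43% against 50% (C).

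Presence is the weaker measure in each scenario. The gap is large only near the ceiling, and in the last ITT row it is within simulation error. A proportional-odds shift also moves some patients to grade 0. If the effect lies wholly between grades 1 and 4, presence does not move at all.

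**4. Grade ≥3 alone is no substitute.** With an odds ratio of 0.4 and all treated, its power is 60% (A), 31% (B) and 11% (C), below the ordinal comparison each time.

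**The case against.** The wording is looser than the literal reading suggests. CTCAE is graded, so a reference to it may imply that grades are kept, and the Statistical analyses section does provide for ordinal data. M1 may be only the date on which records covering the treatment period are read. An article may leave both details to the full protocol. This stands in part: the text is ambiguous and does not exclude grading. But what it does state is presence, and the schedule gives tolerability its own time points without M0.

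A reader might infer more than the documents support:

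- **That the endpoint is saturated and can hardly show a benefit.** No symptom rates are given. The Background says only that treatment can cause such effects, and aspiration is not in its list. The cohort mixes RT alone with CRT and BRT. If M1 is the state at 12 weeks, some acute symptoms may have eased, which argues against a ceiling.
- **That tolerability as a whole fails.** Completion and adjustment are not presence variables and can have no M0 value.
- **That the missing M0 value biases the comparison.** Randomisation immediately follows the baseline measurement, so earlier symptoms are balanced in expectation. The cost is noise and mislabelling.
- **That completion is wrongly repeated or pooled.** The schedule covers tolerability as a whole and does not say that completion is re-analysed at M2 and M3. It is a percentage of each patient's own schedule.
- **That the scoring rule alone would produce a null result.** Refusal accounts for much of the low ITT power, and ordinal grade reaches only 13% to 17% in the diluted scenarios.

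One objection bears on the remedy. The investigator who collects the data knows the allocation, and grading from notes needs more judgement than recording presence.

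**Conclusion.** The point holds as a weakness in how a secondary outcome is fixed. Followed literally, the toxicity variable discards severity, leaves its time window open and cannot separate tumour symptoms from new toxicity. Under the assumed distributions and an odds ratio of 0.4 with everyone treated, the power lost against ordinal grade runs from 62 points (75 − 13) at 95% control presence to 6 points (73 − 67) at 60%. At 36% acceptance it runs from 13 points (16 − 3) to about 1, with low power either way. These figures rest on assumed rates, a proportional-odds effect and no drop-out. The case for change is therefore mainly that severity becomes visible and interpretable. It does not rest on a promise of adequate power. The ITT comparison is not biased, and the 6MWT analysis and the 112 patients are unaffected.

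**What to change.** State in the outcome definition, before extraction begins, that for each of the six items the following are taken from the same medical records:

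- the CTCAE grade at M0;
- the worst CTCAE grade from the first fraction to M1;
- the grade at M2 and at M3.

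Compare the worst grade between randomised groups as ordinal data with the Mann-Whitney test already in the plan. Report the M0 grade alongside, and show grade ≥3 as a descriptive proportion. Completion and adjustment can stay as they are.

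The cost is somewhat more chart abstraction, with no extra visit or procedure. Routine notes will not always carry a grade. Because the plan discards missing cases analysis by analysis, ungraded items should be flagged and counted by arm. Since the data collector is unblinded, grades documented by the treating clinicians should be used where available.

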### Participants

At least 112 patients will be recruited at Instituut Verbeeten, Tilburg, the Netherlands. This hospital is specialized in treating patients with HNC of which approximately 100 patients are treated with (C/B)RT yearly. Patients with HNC scheduled for (C/B)RT will be recruited by the radiation oncologist. First, patients will receive a letter explaining the study aims and procedures. Second, patients who have expressed their interest will be contacted by the local investigator and procedures will be explained in more detail. When a patient agrees, a baseline visit will be scheduled to obtain written IC and perform baseline evaluation measurements.

Patients treated with RT receive 30 times 2,2/2,1gray (Gy). Patients treated with CRT or BRT will receive seven times Cisplatin or Nivolumab combined with 35 times 2 Gy RT. This treatment will be adapted when necessary. All patients with HNC receive advices based on the ‘Dutch physical activity guideline’ [28]. Just before and during (C/B)RT, nutritional care is provided by a dietician on a weekly basis, focusing on optimal energy balance and prevention of negative energy balance.

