### Inclusion and exclusion criteria

In order to be eligible to participate in this study, a patient must meet the following inclusion criteria: 1) patients with HNC who are scheduled for (C/B)RT, 2) ≥ 18 years of age, 3) sufficient Dutch writing and reading skills, 4) a Karnofsky performance status (KPS) > 60 [29], 5) able to walk ≥ 60 m without a mobility aid, and 6) no contraindication for physical activity as measured with the physical activity readiness questionnaire (PAR-Q) [30]. Patients who meet any of the following exclusion criteria will be excluded from participation in this study: (1) recurrence of HNC and/or (2) secondary HNC.

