### Sample size

The sample size calculation is based on the primary outcome, the 6MWT. The power of the study is set on 80% (ß), using differences between two independent means with a 0.05 two-sided significance level. For calculation of the sample size, G*Power 3.1.9.2. was used [31]. Means and standard deviations (SDs) of the 6MWT of the study of Samuel et al. [19] were used. The first mean (SD) [483.16 (88.24)] is of patients with HNC who received the exercise intervention during (C/B)RT and the second mean (SD) [374.52 (110.26)] is of patients with HNC who received usual exercise care during (C/B)RT. Based on this, an effect size of 1.09 was calculated, which resulted in a sample size of 15 patients needed to undergo the PEI. We expect a drop-out of 24% as stated in the study of Samuel et al. [19]. Therefore, 20 patients need to be included in the PEI group. A feasibility study for PEI for patients with HNC in a Dutch population showed that 36% of the approached patients signed IC [13]. To include enough patients, a bigger sample size is needed. Using the expected participation percentage of 36%, a sample size of 56 is needed for the PEI group. Randomisation will be done in a 1:1 ratio so also 56 patients are needed in the control group. In total, 112 patients are needed. With the TwiCs design, two subgroups will arise in the PEI group, consisting of patients who accept and patients who refuse to undergo the PEI [26]. This type of non-compliance (refusal of the assigned treatment) will not be identical between the study arms [32]. Therefore, the sample size calculation will be revised when the real acceptance rate of the PEI differs from the initially estimated acceptance rate, before the end of the study [33].

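### The one-year cost difference, on its natural reading, includes the pre-scheduled (C/B)RT course without adjustment for planned regimen, which adds avoidable chance variation (not bias) to the ICER numerator

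*Protocol article*

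**What the plan says.** All references are to the protocol article.

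- **Cost input (Secondary outcomes):** "To assess health related costs, a cost-effectiveness analysis will be performed for one year. Treatment data will be retrieved from medical records". No list of cost items is given. The same paragraph takes completion and adjustment of (C/B)RT from the medical records as tolerability outcomes.
- **Estimator (Statistical analyses):** the ICER "will be calculated as the difference in costs divided by the difference in QALYs between groups". No adjustment for regimen is mentioned.
- **Regimens (Participants):** RT alone is 30 fractions. For the others, "Patients treated with CRT or BRT will receive seven times Cisplatin or Nivolumab combined with 35 times 2 Gy RT". The section adds that treatment may be adapted where needed. The Discussion says the mixture of treatments is intended.
- **Timing:** the first inclusion criterion is "patients with HNC who are scheduled for (C/B)RT". Type of treatment is recorded at M0 (Measurements), and allocation follows the baseline measurement (Randomisation and blinding).
- **Allocation (Randomisation and blinding):** one box of 112 envelopes, 56 of each kind. No stratification by regimen is described.

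**The concern.** Which course a patient is scheduled to receive is settled before the envelope is opened, so the exercise programme cannot influence it. What the programme can influence is departure from that schedule and other care. If the full course is costed and arm means are simply subtracted, the cost difference also reflects how many systemic-therapy patients happened to fall in each arm. That part says nothing about exercise.

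The Background presents cost-effectiveness as information that hospitals and insurers need, and the Discussion stresses that this is the first such evaluation. The programme itself is inexpensive per invited patient because only about a third are expected to accept. A modest chance imbalance in an expensive item can therefore be as large as the quantity of interest.

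**Working it through.** **1. The plan's own figure.** The documents give no cost, regimen-share or ICER figure, so the sample size is the figure to reproduce, because it supplies the 56 per arm and the 36% used below.

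- Pooled SD = sqrt((88.24² + 110.26²)/2) = 99.86. d = (483.16 − 374.52)/99.86 = 1.088.
- A two-sample t-test at 5% two-sided and 80% power needs 14.29, rounded up to 15. This agrees with the text: "an effect size of 1.09 was calculated, which resulted in a sample size of 15 patients needed to undergo the PEI".
- 15/(1 − 0.24) = 19.7, rounded up to 20. 20/0.36 = 55.6, rounded up to 56. 2 × 56 = 112. Reproduced.

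**2. Chance difference in regimen mix.** Let p be the share on systemic therapy (assumed 30-50%; not in the documents) and n the number per arm. SD of the difference in shares = sqrt(2p(1 − p)/n).

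| p | n = 56 | n = 156 |
|---|---|---|
| 0.3 | 0.0866 | 0.0519 |
| 0.4 | 0.0926 | 0.0555 |
| 0.5 | 0.0945 | 0.0566 |

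The hypergeometric distribution for 56/56 envelopes gives nearly the same SDs (0.0873, 0.0931, 0.0949). It puts an imbalance of 10 points or more at about 25-35% probability over this range of p. The second column applies if recruitment continues until 56 patients accept, as Randomisation and blinding also says: 56/0.36 = 155.6, about 156 invited, with as many controls.

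**3. Programme cost per invited patient.** 10 weeks × 2 supervised sessions = 20 sessions. 20 × 0.36 = 7.2 session prices, assuming that those who accept attend every session. At an assumed EUR 50 per session this is EUR 360.

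**4. Break-even.** Let K be the extra cost of a systemic regimen over RT alone. One SD of mix equals the programme cost when K = 7.2/SD session prices.

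- n = 56: 7.2/0.0945 = 76 to 7.2/0.0866 = 83 session prices. At EUR 50 this is about EUR 3,800-4,200.
- n = 156: 7.2/0.0566 = 127 to 7.2/0.0519 = 139 session prices. At EUR 50 this is about EUR 6,400-6,900.

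The instrumental variable estimate divides the same between-arm difference by the acceptance rate, so noise and programme cost scale together and the break-even is unchanged.

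**5. Sensitivity to K at 56 per arm** (p = 0.3 to 0.5). One SD of mix = K × 0.0866 to K × 0.0945, against EUR 360:

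- K = EUR 2,000: EUR 173-189, about half the programme cost.
- K = EUR 5,000: EUR 433-472.
- K = EUR 10,000: EUR 866-945.

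**The case against.** The strongest counter-argument is that the premise is inferred. The article does not list cost items, and the reference to treatment data would also fit costing only departures from schedule. An article may leave the item list to an economic plan that is not shown, and dividing a cost difference by a QALY difference is simply the definition of an ICER and does not exclude adjustment. This stands in part. Inclusion of the course is the natural reading, since the article ordinarily uses the word treatment for (C/B)RT and the year contains the course, but it is not a stated fact.

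Three stronger readings might be inferred, and the documents do not support them:

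- **That the ICER numerator is biased.** It is not. The regimen precedes a random draw, so its expected contribution to the difference is zero. The cost is precision only.
- **That (C/B)RT costs are beyond the programme's reach and should all be removed.** Only the scheduled course is fixed. Completion and adjustment are outcomes that the programme is meant to improve, so stripping out all (C/B)RT cost could remove a real effect.
- **That regimen mix will swamp the programme's cost or reverse its sign.** That depends on prices the documents do not give and on the number per arm. Take EUR 50 per session, a 40% share, programme cost as the only true difference and mix as the only noise. The chance of sign reversal at 56 per arm is then about 3%, 22% and 35% for K = EUR 2,000, 5,000 and 10,000. At 156 per arm it is about 0.1%, 10% and 26%. Savings elsewhere and other cost variation are ignored, so these figures are illustrative only.

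It is also fair to say that leaving out the scheduled course is not the only remedy. Regression adjustment or stratified comparison by planned regimen does the same job and keeps total cost as the main figure. It also deals with other care whose cost varies by regimen, which leaving out the course does not.

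**Conclusion.** The point holds as a cheap gain in precision, not as a demonstrated error. As described, neither the allocation nor the ICER takes account of a cost driver that is known at baseline, differs materially between patients and cannot be changed by allocation.

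If the scheduled course is costed, one SD of chance mix is 8.7-9.4 points at 56 per arm (5.2-5.7 at about 156). It matches the supervised programme's cost per invited patient at a regimen cost gap of about 76-83 session prices (127-139 at about 156 per arm). With a gap near EUR 2,000 and EUR 50 sessions the effect is small; with a gap of EUR 10,000 it exceeds the programme cost on either recruitment reading (0.0519 × 10,000 = EUR 519 at the least, against EUR 360).

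The conclusion rests on the natural reading of the cost input, on assumed systemic shares of 30-50% and on assumed prices. The 36% acceptance, 20 sessions and 56 per arm are the plan's own. If an economic plan already adjusts for planned regimen or leaves out the scheduled course, one sentence in the article closes the matter.

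**What to change.** Add to Secondary outcomes and Statistical analyses one of two statements, which are equivalent in expectation:

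1. The between-group cost difference used in the ICER is adjusted for the (C/B)RT regimen planned at M0.
2. The cost of the course scheduled at M0 is left out of the incremental cost, while departures from that schedule (fractions or systemic administrations omitted, added or replaced), the PEI and all other health care are costed.

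In either case, report the unadjusted difference in total one-year cost alongside. The first option is preferable if total cost is to remain the main figure.

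No new data are needed: type of treatment is recorded at M0, and completion and adjustment are already extracted for tolerability. The price is a sentence of analysis text and one extra table. Under the second option there is a further downside: the main figure is no longer total one-year cost.
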